## Methods/Design

### Ethical approval and trial registration

The study is carried out in compliance with the Helsinki Declaration. The local ethics committee of the Maastricht University Medical Centre has approved the study protocol, patient information letter, and the informed consent forms. Informed consent is obtained and signed by the patient prior to the screening session, after the patient is fully informed about the study and the procedures. The Parkin’Play study is registered in the Dutch trial registration under registration number NTR5637.

### Study design

The Parkin’Play study is a multicenter phase-II open-randomized controlled study that aims to recruit 222 patients with Parkinson’s disease with PD-MCI. Patients are randomly assigned to the intervention (cognitive training) or the control group (waiting list). All participants will undergo three assessments (t = 0, t = 1, and t = 2), which consist of neuropsychological assessments and questionnaires. In 20 patients from each group (total *n* = 40) two fMRI scans will be obtained (t = 0 and t = 1). The duration of the main intervention will be 12 weeks. In order to investigate the compliance and attractiveness of the health game, patients will be given the opportunity to continue playing for an additional 12 weeks (Fig. 1). The study will be analysed based on an intention-to-treat approach and results will be published on behalf of the Parkin’Play investigators.

**Fig. 1 Fig1:**
[figure not shown]
Design of the Parkin'Play study

### Intervention

The total duration of the intervention will be 12 weeks for both groups, with a voluntary extension of the cognitive training for an additional 12 weeks.

#### Cognitive training (intervention group)

The intervention consists of a combination of two software products. To give people insight into their cognitive profile and tailor the intervention towards an individuals’ weaknesses, the participants’ cognitive functions will be assessed using an online assessment tool: MyCognition Quotient (MyCQ™). MyCQ™ is a cognitive assessment tool developed by the company MyCognition. Through ten individual tests, this assessment specifically evaluates the patients’ capabilities in five core cognitive domains: attention, psychomotor speed, working memory, episodic memory, and executive function, consistent with other standard cognitive assessment targeted on Parkinson Disease [20, 21], and with the main neuropsychological domains normally considered as being affected by PD-MCI [22]. MyCQ™ is a 30-min assessment, which provides a personalized cognition score for each individual and a profile of strengths or weaknesses across the five core cognitive domains assessed. The individual tests that comprise the MyCQ™ assessment are based on validated paradigms and they are considered to be revised versions of paradigms that are commonly employed in the assessment of human cognition (see Table 1). The MyCQ™ was compared to the Cambridge Neuropsychological Automated Test Battery (CANTAB) in a population of fifty-five patients with psychiatric disorders [23]. Results indicated that most of the MyCQ™ subtests correlated with the CANTAB subtests of the corresponding domain.

**Table 1 Tab1:** Individual MyCQ™ tests listed with test equivalents

	MyCQ™ Test	Cognitive domains measures	Paper & pencil test equivalent	Computerised test equivalent
1	Simple Reaction Time	Psychomotor speed	Donders Type A	Detection
2	Choice Reaction Time	Attention	Donders Type B	Identification
3	Go/No Go^a^	Inhibition	Donders Type C	-
4	Verbal recognition memory	Episodic memory	Rey Auditory Verbal Learning Test	CDR Word Recognition
5	Visual recognition memory	Episodic memory	Benton Visual Retention Test	CDR Picture Recognition
6	1-Back^a^	Working memory	-	One Back
7	2-Back^a^	Working memory	-	Two Back
8	Trail Making A	Praxis/psychomotor speed	Trail Making Test Part A	Chase Test
9	Trail Making B^a^	Praxis/psychomotor speed/set shifting	Trail Making Test Part B	Groton Maze Learning Test
10	Coding^a^	Psychomotor speed/attention	Digit Symbol Substitution Test	-

^a^Also indexes elements of executive function

The second product is a custom-made and web-based cognitive training AquaSnap that was built with input from experts of both Radboud University Medical Center and Maastricht University Medical Center. The adaptive cognitive training aims at exercising the cognitive domains of attention, working memory, episodic memory, psychomotor speed and executive function. In AquaSnap, played online on a PC/laptop or Apple iPad, a player is required to explore the ocean in an underwater rover and complete specific tasks by taking pictures of fish. The pictures are worth currency, which can be used to dive deeper into the sea to discover different aquatic environments with rarer fish. The MyCQ™ assessment is carried out monthly and according to an individuals’ profile, AquaSnap adapts the speed and difficulty level of the game. The lower a player’s MyCQ™ score, the more training tasks they need to complete in that specific domain. Each cognitive domain is mainly trained by a particular training loop, while some domains are trained across different tasks (see Table 2). The game develops on different structural levels. At the basic structural level there are the loops, which corresponds to the five first tasks in Table 2. The loops are organized in underwater dives, in which the player undergoes a set of loops. At the Ocean map level, users have to organise their dive in order to both achieve the proposed mission and to discover new areas. The progress of the players on the map, and consequently the growth of difficulty in the training game depend on the coins the players are able to collect during their dives. In this way the game adapts its difficulty to the level of progression reached by the player (Fig. 2). Additionally, as mentioned above, the intensity of the training depends on the individual MyCQ™ scores, as the number of loops for each type of task depends on the score obtained on each cognitive domain. In this way, more impaired domains will receive more intensive training.

**Table 2 Tab2:** Individual tasks in AquaSnap and trained domains

	AquaSnap task	Description	Cognitive domain
1	Memory shot	Remember the position of the glowing fish in the loop	Working memory
2	Quick shot	Snap the fish as soon as you see it	Processing speed and attention
3	Careful quick shot	Snap the fish as soon as you see it, but be careful not to snap the shocking flash	Attention and executive function (inhibition)
4	Group shot	Snap the group of fish all together	Attention and processing speed
5	Fish Tracker	Remember which fish are glowing after they change position	Working memory
6	Oceanic survey	Remember which fish have you seen at the end of the dive	Episodic memory
7	Missions and map exploration	Achieve the goals proposed by the daily missions and try to discover new areas on the ocean map	Executive function (planning and organizing)

**Fig. 2 Fig2:**
[figure not shown]
Feedback loops regulating the difficulty and pace of the AquaSnap training

The duration of the cognitive training period is set at 12 weeks with a cumulative duration of 18 h, divided over 36 sessions. In other cognitive training studies, the mean cumulative duration was 17,6 h with a range between 5 and 42 h and the mean training period was 9 weeks with a range between 4 and 24 weeks [10, 11, 24–26].

Time spent per day on gaming will be recorded automatically. There will no pre-set time limits in order to investigate the attractiveness of the games as well as the possibility of testing for addictive behaviour in post-hoc analyses. To prevent attrition due to an inadequate level of difficulty (i.e. too high or too low), coaches will contact the patients every two weeks in the first month to adjust the levels accordingly.

#### Waiting list (control group)

The control group is designed as a waiting list group in order to increase compliance. The participants are required to perform the MyCQ™ assessment monthly. For motivational purposes, the control group is offered to take part in a deferred intervention after 12 weeks (e.g. from week 12 until 24), with the same intensity as the intervention group in the first 12 weeks.

#### Drop-outs and adverse events

Patients who drop out will be encouraged to complete the follow-up measurements. All unwanted and harmful outcomes spontaneously reported by the patients, that may or not be related to the treatment (adverse events), will be recorded according to section 10, subsection 1 of the Dutch Research Involving Human Subjects Act (WMO). Addiction to playing the game will be monitored by recording the amount of playing time and the BIS-11 scoring that measures changes in impulsivity. In case of a serious adverse event, the Ethics committee and relevant authorities (Toetsingonline and principal investigator) will be notified immediately.

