### Randomization and blinding

After the baseline measurements are performed, participants will be randomly assigned to one of two groups: the Intervention group (IG), or the Control group placed on a waiting list (CG), in a 1:1 ratio. Randomisation (minimisation) will be performed by the Clinical Trial Centre Maastricht (not formally involved in the study or assessments) using the software package ALEA (Formsvision BV). Stratification factors include site location (Maastricht, Nijmegen, or Heerlen) and age group (<60 and > =60 years old). The study is an open-randomised controlled trial, so there will be no blinding for treatment allocation. Nonetheless, all follow-up measurements will be assessed by blinded outcome assessors. Patients will be enrolled by a coordinating investigator, who assigns patients to the intervention groups.

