### Study activities

Enrolment will take place in the weeks prior to baseline assessment, except for the additional inclusion assessments (see Table 4). The following demographics and general variables are collected at baseline: date of birth, sex, educational level, age at onset, disease duration, and details on Parkinson medication (i.e., drug name, dose, frequency, levodopa equivalence). Details on Parkinson medication will also be collected at both follow-up measurements. Randomization will be performed after the baseline assessment. Primary and additional outcome assessments will be performed at baseline, after 12 and after 24 weeks follow up. The additional fMRI scans will be performed at baseline and after 12 weeks, matching the primary outcome assessments. The intervention group will be required to play the health game from start of the intervention until week 12 for at least 36 sessions of 30 min (three times a week). After week 12, both the intervention as well as the control group will be allowed to continue playing the health game free of choice. All patients will be examined in their on-state.

**Table 4 Tab4:** Study schedule and assessments

	Timepoint →	-*t* _1_	*t* _0_			*t* _1_	*t* _2_
	Visit # →	0	1			2	3
	Week # →	-1 to -3	0	4	8	12	24
ENROLMENT: Screening & inclusion assessments							
Regular clinical intake		X					
Demographics		X					
Inclusion/exclusion		X					
National Adult Reading Task			X				
Montreal Cognitive Assessment			X				
Epworth Sleepiness			X				
Levodopa equivalent dose (LED)			X			X	X
ASSESSMENTS: Primary outcomes							
Standard neuropsychological battery			X			X	X
MyCQ™ assessment			X	X	X	X	X
Additional outcomes							
Motor function (UPDRS part III)			X			X	X
Self-report questionnaires			X			X	X
Parkinson Disease Questionnaire-39			X			X	X
Pre-Rasch-built Overall Disability Scale			X			X	X
fMRI exclusion criteria		X					
fMRI scan			X			X	
INTERVENTIONS							
Randomization			X				
Game playing (36 sessions of 30 min)			X	X	X	*X*	*X*

Only for subset of patients (*n* = 40)

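### Adverse events are recorded only when volunteered, and the only described human contact before week 12 is in the trained arm, so any comparison of event counts risks a modest bias

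*Protocol article*

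**What the plan says.** Under Drop-outs and adverse events, the protocol article sets the capture rule. What is recorded is "All unwanted and harmful outcomes spontaneously reported by the patients", whether or not related to treatment. One specific harm is tracked separately: "Addiction to playing the game will be monitored by recording the amount of playing time and the BIS-11 scoring that measures changes in impulsivity".

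Under Cognitive training (intervention group), the text after Fig. 2 says that "coaches will contact the patients every two weeks in the first month to adjust the levels accordingly". The stated purpose is to prevent attrition caused by a badly set difficulty level.

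Under Waiting list (control group), the requirement before week 12 is this: "The participants are required to perform the MyCQ™ assessment monthly". The Outcome measures section describes that test as web-based. The waiting-list section also offers controls the game from week 12 to week 24.

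Study activities gives the shared visits: "Primary and additional outcome assessments will be performed at baseline, after 12 and after 24 weeks follow up". In Table 4, weeks 4 and 8 carry only the MyCQ and game playing.

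Randomization and blinding states: "The study is an open-randomised controlled trial, so there will be no blinding for treatment allocation". Follow-up outcome assessors are blinded.

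The Statistical analysis procedure section names no between-arm comparison of adverse events. Harm appears there once, where the study may be ended after the interim analysis (40 patients through 12 weeks) if training proves particularly harmful, in consultation with the ethics committee. The data that would define harm are not named.

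**The concern.** When events count only if the patient brings them up, the number recorded depends on how many occasions the patient has to do so. As written, those occasions differ by arm during weeks 0–12, which is the only period when one arm trains and the other does not. Adjusting game levels has no meaning for a patient who is not playing, so the purpose of the coach contact, as well as its place in the text, points to the trained arm alone.

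Two features of this trial add to the problem. Patients are unblinded, so a trained patient may connect a complaint with the game and mention it to the coach. Participants also have mild cognitive impairment, and the Background notes that memory deficits are frequent, so unprompted recall at week 12 is likely to miss events in both arms. The second feature causes under-counting, not imbalance.

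At stake is how the safety results can be read: a modest excess of reported events in the trained arm could not be told apart from a difference in contact.

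**Working it through.** The documents state no figure for adverse events, so there is nothing to reproduce. The check has two parts.

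**1. Occasions to report, randomisation to week 12**

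| | Trained arm | Waiting list |
|---|---|---|
| Coach contact, weeks 0–4 | about 2 (every two weeks for one month: 4/2) | none described |
| Weeks 4 and 8 | online MyCQ | online MyCQ |
| Week-12 assessment | 1 | 1 |
| Human contacts described | about 3 | 1 |

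The extra occasions all fall in the first month. An event that starts after week 4 has the same single occasion in both arms.

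**2. Size, by illustration**

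All values here are assumptions:
- the true event risk is the same in both arms;
- events start evenly over 12 weeks;
- coach contacts fall at weeks 2 and 4;
- both arms share one week-12 visit;
- a patient who has had an event mentions it with probability p at each later contact, independently.

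The chance that an event is captured over k contacts is 1 − (1 − p)^k. In the trained arm:
- weeks 0–2: 2/12 = 1/6 of events, k = 3;
- weeks 2–4: 1/6 of events, k = 2;
- weeks 4–12: 8/12 = 4/6 of events, k = 1.

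In the control arm k = 1 throughout, so capture equals p. Trained-arm capture is [c(3) + c(2) + 4·c(1)] / 6, where c(k) is the formula above.

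| p | c(3) | c(2) | c(1) | Trained arm | Control | Ratio |
|---|---|---|---|---|---|---|
| 0.1 | 0.271 | 0.190 | 0.100 | (0.271 + 0.190 + 0.400)/6 = 0.1435 | 0.100 | 1.4 |
| 0.2 | 0.488 | 0.360 | 0.200 | (0.488 + 0.360 + 0.800)/6 = 0.275 | 0.200 | 1.4 |
| 0.5 | 0.875 | 0.750 | 0.500 | (0.875 + 0.750 + 2.000)/6 = 0.604 | 0.500 | 1.2 |

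In patients: with 111 per arm, an assumed true risk of 10% (11.1 patients with an event) and p = 0.2, the trained arm would record 11.1 × 0.275 ≈ 3.0 and the control arm 11.1 × 0.200 ≈ 2.2.

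The ratio would be higher if events cluster early, or if recall at week 12 is poorer than recall at a two-week contact. It would be lower if patients in both arms often report outside scheduled contacts. If both arms report equally, there is no bias.

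**The case against.** Several points on the other side stand.

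- **No harm comparison is stated.** The article says that adverse events are recorded under Dutch law and that serious events are notified at once. Neither depends on comparing arms. A reader might infer that the planned harm comparison, or the ethics committee's interim consultation, rests on these counts. The documents do not say so: the interim analysis follows the 12-week assessments, and harm there may mean cognition.
- **The contact is limited.** It covers the first month only, about two contacts, and its purpose is to set difficulty. That controls have no such contact is inferred from where the sentence sits and what it is for; the waiting-list section does not rule out other contact.
- **Some harm is measured systematically.** Playing time and the BIS-11 cover addiction. The self-report questionnaires and motor scale are collected in both arms at weeks 12 and 24. None of these replaces general adverse-event capture, but harm is not left wholly to volunteering.
- **The article is condensed.** It refers to operating procedures and manuals that may describe how patients are asked.

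The last point does not dispose of the matter. The article does not merely omit the method; it states that events are those reported spontaneously. The others limit the claim to a risk for any comparison that is made, and limit its size.

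**Conclusion.** The point holds in a limited form. As written, capture is passive, patients are unblinded, and the described opportunities to report before week 12 are unequal. Any between-arm comparison of adverse events, or any use of them in the interim harm decision, would be at risk of a modest bias towards more reported events in the trained arm. Under the stated assumptions the capture ratio is about 1.4 to 1.2 for p from 0.1 to 0.5. The true size cannot be derived from the documents.

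A reader might compare three contacts with one and infer a 2.7-fold (0.271/0.100) to 1.75-fold (0.875/0.500) excess. That would apply only if every event began before the first coach contact. The coach contacts end after the first month, and events after week 4 have equal opportunity, so the documents do not support it. Nor do they support saying that a planned harm analysis is biased, since none is stated.

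Priority is low to moderate. The primary efficacy result is not affected.

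**What to change.** Ask both arms the same open, non-leading question about new or worsened problems at the same times.

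- **At minimum**, put it in the digital questionnaires that both arms already complete at weeks 12 and 24.
- **If feasible**, also ask it at weeks 4 and 8 alongside the MyCQ, which would shorten the recall period. This is optional because the MyCQ is a company's product and adding an item may mean changing it.
- Have answers reviewed by staff other than the blinded outcome assessors.
- Keep recording volunteered events, and label every event by source: solicited, spontaneous or coach contact.
- Base any between-arm comparison, including one put to the ethics committee at the interim, on the common solicited items for weeks 0–12.
- Report weeks 12–24 separately, because controls may then be playing.

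The cost is one item in existing forms, one source field on the adverse-event form, and more minor events to record and review. No visits are added.

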#### Medication adjustments

All participants are asked to keep their medication stable during the intervention period. Nonetheless, if medication changes are presumed necessary by the treating neurologist, they are allowed to do so. Any changes in medication will be noted in the case report form.

### Study population

In- and exclusion criteria are shown in Table 3. Patients who are eligible for participating in the study have PD diagnosed by an experienced neurologist, with Hoehn and Yahr stages I–III, and are aged between 40 and 75 years. Furthermore, they have cognitive impairment but no dementia. Neuropsychological assessment including a global measure and a limited battery of standard tests will be used to assess whether MCI is present in accordance with the Level I criteria for the diagnosis of PD-MCI by Litvan et al. [27]. Patients must be on relatively stable dopaminergic medication for at least three months prior to inclusion, or the change in medication does not influence cognition. Patients should not receive any other cognitive therapy during the study period. Also, gamers who play any type of computer games more than one hour per week in the preceding year are excluded from participation.

**Table 3 Tab3:** In- and exclusion criteria

Inclusion criteria	Exclusion criteria
Idiopathic Parkinson’s disease diagnosed by a neurologist	Medication affecting cognition (such as anticholinergic drugs, benzodiazepine and methylfenidate)
Hoehn & Yahr stage ≤3	Other medical conditions: o Advanced problems in cognitive functioning (MoCA <19/30) o Dementia o Active depression or psychosis and/or treatment with anti-depressant or anti-psychotic drugs o History of active thyroid disease, stroke with residual deficits, severe hypertension or diabetes or head trauma interfering in cognition
Age 40-75 years	Severe auditory of visual deficits
Mild cognitive impairment according to MDS (MCI Level 1 criteria)	No internet at home
Relatively stable dopaminergic medication dose for at least three months prior to the study, or change in medication does not influence cognition. Deemed unlikely to start or stop treatment within the next three months.	fMRI sub-study: o Metal in the body o Claustrophobia

### Recruitment and setting

The treating neurologist will evaluate eligibility of patients using a checklist. After eligible patients have been informed about the study and have agreed to participate, they will be invited for a screening assessment. Informed consent is signed prior to the screening assessment. The inclusion period for the Parkin’Play study will last 18 months. In order to reach target sample size, neurologists from Maastricht University Medical Center, Radboud University Medical Center Nijmegen, and Zuyderland Medical Center Heerlen will be involved in recruitment. Participants are currently being recruited and enrolled. For practical reasons, only patients from Maastricht University Medical Center will be asked to join the fMRI sub-study, prior to the screening assessment. We stop including fMRI participants when the goal of 20 patients per arm is reached.

### Randomization and blinding

After the baseline measurements are performed, participants will be randomly assigned to one of two groups: the Intervention group (IG), or the Control group placed on a waiting list (CG), in a 1:1 ratio. Randomisation (minimisation) will be performed by the Clinical Trial Centre Maastricht (not formally involved in the study or assessments) using the software package ALEA (Formsvision BV). Stratification factors include site location (Maastricht, Nijmegen, or Heerlen) and age group (<60 and > =60 years old). The study is an open-randomised controlled trial, so there will be no blinding for treatment allocation. Nonetheless, all follow-up measurements will be assessed by blinded outcome assessors. Patients will be enrolled by a coordinating investigator, who assigns patients to the intervention groups.

